# Anterior quadratus lumborum block for postoperative recovery after total hip arthroplasty: a study protocol for a single-center, double-blind, randomized controlled trial

**DOI:** 10.1186/s13063-020-4090-0

**Published:** 2020-02-05

**Keywords:** Anterior quadratus lumborum block, Hip osteoarthritis, Peripheral nerve block, Postoperative pain, Regional anesthesia, Total hip arthroplasty

## Abstract

**Background:**

Appropriate pain management is essential to improve the postoperative recovery after total hip arthroplasty (THA). Various case reports have indicated that anterior quadratus lumborum block (QLB) provides effective postoperative analgesia in lower limb surgeries. However, few randomized controlled trials have confirmed the efficacy of anterior QLB for lower limb surgeries. The aim of this single-center, double-blind, randomized controlled trial is to confirm the efficacy of anterior QLB for postoperative recovery after THA.

**Methods:**

The participants will be randomly assigned to either the anterior QLB or placebo groups, using a set of random numbers for the allocation sequence. Only pharmacists will be aware of the allocations; other investigators will be blinded until study completion. After induction of general anesthesia, anterior QLB will be performed by using 0.25% levobupivacaine or normal saline. Fentanyl will be administered according to blood pressure change during the surgery. The primary outcome will be the quality of recovery 40 score (QoR-40). Secondary outcomes will include the visual analog scale score of pain intensity at rest and movement, intraoperative and postoperative doses of fentanyl, and incidence of postoperative nausea and vomiting. Statistical analysis will be performed by using the Student’s *t* test, Mann–Whitney *U* test, and Fisher’s exact test as appropriate. A *P* value of less than 0.05 will be considered statistically significant.

**Discussion:**

The results of our study will reveal whether anterior QLB is effective for postoperative recovery after THA.

**Trial registration:**

UMIN Clinical Trials Registry, UMIN000032255. Registered on 15 April 2018.

## 1. Background

Hip osteoarthritis is a disease that causes pain and restricts the range of motion as the hip joint deforms. In Japan, the prevalence of hip osteoarthritis is estimated at 1.0%–4.3% and the number of patients with hip osteoarthritis reaches 1.2–5.1 million [1]. The treatment options for patients with hip osteoarthritis include conservative therapies and surgery. Conservative therapies include patient education, hyperthermia treatment, pharmacological treatment using non-steroidal anti-inflammatory drugs, and physical therapy treatment tailored to the patient’s condition. Surgery is recommended for patients whose condition does not improve with conservative therapies or for those with advanced disease [2]. Recently, total hip arthroplasty (THA) has been widely performed; about 23,000 THA surgeries are performed every year in Japan [3].

THA causes moderate to severe postoperative pain, and inadequate perioperative analgesia management delays ambulation and decreases the quality of postoperative recovery [4]. Opioids are commonly used for postoperative analgesia in various surgeries but their use is associated with respiratory depression or postoperative nausea and vomiting (PONV) and impaired quality of recovery. Therefore, regional anesthesia is often preferred.

Regional anesthesia for postoperative analgesia in THA includes epidural anesthesia and peripheral nerve blocks. Although epidural anesthesia has been used for postoperative pain management in THA, it has become restricted as perioperative antithrombotic drugs are generally used for orthopedic patients. Currently, many types of peripheral nerve blocks, such as the femoral nerve block (FNB) and the lumbar plexus block (LPB), are used for THA surgeries. Peripheral nerve block has been thought to cause less serious complications than epidural anesthesia [5]. The efficacy of FNB for THA has been reported in many studies in the past few decades [6, 7]. However, it has been suggested that FNB might not provide sufficient postoperative analgesia for THA because the hip joint is innervated not only by the femoral nerve but also by other nerves such as the obturator nerve and the sciatic nerve. LPB is a procedure during which a local anesthetic is administered around the lumbar nerve roots so that the femoral nerve, obturator nerve, and lateral femoral cutaneous nerve are blocked. Although LPB provides adequate postoperative analgesia for THA [8], it has a high potential of serious complications such as nerve injury and hematoma [9] because the needle tip should be advanced close to the nerves.

The quadratus lumborum block (QLB), first reported by Blanco in 2007, is a compartment block procedure during which a local anesthetic is injected into the muscle plane of the quadratus lumborum muscle under ultrasound guidance [10]. Currently, QLB is divided into four types based on the injection point of the local anesthetic: lateral, anterior, posterior, and intramuscular QLB. QLB is widely used for various types of abdominal surgeries [11]. In the anterior QLB, described by Børglum *et al*. in 2013, a local anesthetic is injected between the quadratus lumborum muscle and the psoas major muscle [12]. Although anterior QLB was first reported for analgesia in abdominal surgeries, it could provide analgesia for lower limb surgeries by spreading the local anesthetic around the psoas major muscle and blocking lumbar nerve roots such as in LPB. Cadaveric studies showed the spread of a dye around the lumbar plexus by anterior QLB [13, 14]. Anterior QLB may block not only the femoral nerve but also the obturator nerve and the lateral femoral cutaneous nerve, thus possibly providing more effective analgesia in THA than FNB. Additionally, because the needle tip is distant from the lumbar nerve roots in anterior QLB, it has a lower risk of nerve injury than LPB. Indeed, reports on serious QLB-related complications are scarce.

The efficacy of anterior QLB for lower limb surgeries has been reported in some case reports [15–17], but no randomized controlled trials (RCTs) have been conducted. Therefore, it remains unclear whether anterior QLB provides sufficient analgesia and improves the quality of postoperative recovery after lower limb surgeries such as THA.

The aim of this single-center, double-blind RCT is to confirm the efficacy of anterior QLB for postoperative recovery after THA. Here, we describe the study protocol for such a trial.

## 2. Methods/Design

### 2.1. Trial design

This study is designed as a single-center, prospective, double-blind RCT. The participants will be randomly assigned to either the anterior QLB group or the placebo group.

### 2.2. Ethics

This study was approved by the institutional review board of Yokohama City University Hospital (B180405008) and was registered with the UMIN Clinical Trials Registry (UMIN000032255, registered on April 15, 2018, https://upload.umin.ac.jp/cgi-open-bin/ctr/ctr_view.cgi?recptno=R000036231). This trial will be performed in accordance with the principles of the Declaration of Helsinki (Edinburgh 2000 version). Written informed consent will be obtained from each participant before enrollment.

### 2.4. Blinding

The pharmacists in the Department of Pharmacy of Yokohama City University Hospital will prepare the syringes containing either 30 mL of 0.25% levobupivacaine (Maruishi Pharmaceutical Co., Tokyo, Japan) or 30 mL of normal saline in accordance with the allocation sequence. The syringes will be labeled “trial drug” and given a number and will be transported to the operating rooms by the drug conveyance in the hospital. The pharmacists in the Department of Pharmacy will participate in the trial only at this stage; therefore, the participants, attending anesthesiologist, surgeons, evaluators, and the researchers will be unaware of the random allocation sequence. The random allocation sequence will not be exposed until the final data analysis report is completed.

### 2.5. Study setting

This trial will be conducted in the Yokohama City University Hospital ([name]).

### 2.6. Eligibility criteria

#### 2.6.2. Inclusion criteria

Patients eligible for the study must comply with all of the following criteria at randomization:
elective unilateral THA;age of at least 20 years;American Society of Anesthesiologists Physical Status (ASA-PS) 1–2;written informed consent to participate in this trial.

#### 2.6.2. Exclusion criteria

revision cases;liver and kidney dysfunction (aspartate aminotransferase of more than 80 IU/L, alanine aminotransferase of more than 80 IU/L, estimated glomerular filtration rate of less than 50 mL/min);coagulopathy (prothrombin time/international normalized ratio of more than 1.50, activated partial thromboplastin time of more than 60 s);body mass index of more than 35;use of a strong opioid, such as morphine or fentanyl;allergy to the study drugs and their components;dementia;cases judged to be inappropriate by the researchers (e.g., cases where the patient has undergone other femoral surgeries such as intramedullary nailing).

Since certain patients with hip osteoarthritis receive tramadol for management of their pain in Japan, we decided to include these patients in our trial and exclude those receiving strong opioids such as morphine or fentanyl.

### 2.7. Interventions

#### 2.7.1. General anesthesia induction and maintenance

When the patient arrives in the operating room, a standard vital monitoring system, which includes electrocardiography equipment, non-invasive blood pressure monitor, and pulse oximeter, will be in place and a 22- or 20-gauge intravenous catheter will be inserted in the patient’s forearm. General anesthesia will be induced with propofol 1.5 mg/kg, fentanyl 3 μg/kg, and rocuronium 0.6 mg/kg; tracheal intubation will be performed. General anesthesia will be maintained using desflurane 3%–5% and remifentanil 0.2 μg/kg per min. The concentration of desflurane and additional use of rocuronium will be left to the discretion of the attending anesthesiologist. If the patient’s blood pressure increases to more than 20% of the baseline blood pressure during surgery, the anesthesiologist will administer fentanyl 50–100 μg and observe the patient for 15 min. On the contrary, if the blood pressure decreases to less than 20% of the baseline blood pressure, the anesthesiologist will administer ephedrine 4–8 mg or phenylephrine 0.05–0.1 mg and observe the patient for 15 min. The attending anesthesiologist will measure the blood pressure every 5 min; in cases with further decline, additional administration of ephedrine or phenylephrine will be permitted.

#### 2.7.2. Anterior QLB procedure

After general anesthesia induction, anterior QLB will be performed in the lateral position. A low-frequency convex probe for the abdomen (2–5 MHz convex probe, Sonosite Edge® rC60xi; Sonosite Canada Inc., Markham, ON, Canada) will be placed horizontally above the iliac crest. On ultrasound, the lumbar vertebral body and transverse process appear as “thumbs up” structures. Additionally, three muscles can be found around the transverse process: the psoas major, erector spinae, and quadratus lumborum muscles. The psoas major is located on the ventral side of the transverse process, the erector spinae is located on the dorsal side of the transverse process, and the quadratus lumborum is located on the lateral side of the transverse process.

After a pre-scan and ultrasound parameter optimization, the probe will be applied by using a sterile technique. A 20-gauge short-bevel needle (Visioplex, Vygon, France) will be inserted in the plane from the posterior edge of the convex probe through the quadratus lumborum in an anteromedial direction. When the needle tip reaches the area between the psoas major and the quadratus lumborum, 30 mL of 0.25% levobupivacaine will be injected in the anterior QLB group; the same amount of normal saline will be injected in the placebo group. Figure 1 shows an ultrasound image of anterior QLB.

#### 2.7.3. Perioperative management of pain and PONV

As multimodal analgesia, 20 mg/kg acetaminophen (maximum of 1000 mg/body) will be administered after the end of surgery and repeated each 6 h until 24 h. From postoperative days 1 to 7, the patients will receive celecoxib 100 mg twice a day. Intravenous fentanyl will be used for patient-controlled analgesia (IV-PCA) using CADD-Solis (Smiths Medical, Grasbrunn, Germany). A bolus injection of 10 μg fentanyl with a 10-min lockout time may be administered for analgesia; continuous infusion of fentanyl will not be considered. In our clinical experience, the pain in most patients may be managed with this protocol. If the patients experience pain, particularly before they start drinking water, flurbiprofen axetil or diclofenac sodium will be administered during the postoperative period. However, in our clinical experience, the incidence of flurbiprofen axetil or diclofenac sodium administration is considerably low.

To prevent PONV, dexamethasone 6.6 mg will be administered before the start of the surgery. Droperidol 0.02 mg/kg or metoclopramide 10 mg may be used according to the postoperative condition. Repeated administration of droperidol and metoclopramide will be permitted in patients continuing to experience PONV.

### 2.8. Outcomes

#### 2.8.1. Primary outcome

The primary outcome will be the Quality of Recovery score 40 (QoR-40) 24 h after surgery. The QoR-40 is a tool that assesses patient-reported outcomes, including quality of life. It was originally developed and validated in Australia in 2000 and is currently used widely as an indicator of postoperative recovery [18, 19]. The QoR-40 is a recovery-specific and patient-rated questionnaire that contains 40 items measuring five dimensions: physical comfort (12 items), emotional state (9 items), physical independence (5 items), psychological support (7 items), and pain (7 items). The total score and subscales of the QoR-40 are measured by using a five-point Likert scale (for positive items: 1 = none of the time, 5 = all of the time; for negative items, the scoring is reversed) and then individual scores are added together; the final score ranges from 40 to 200. In 2011, the Japanese version of the QoR-40 was validated in accordance with standard methods of cultural adaptation and psychometric analysis [20].

#### 2.8.2. Secondary outcomes

The secondary outcomes will be as follows:
visual analog scale (VAS) score of pain intensity at rest and movement at postoperative days 1 and 2; scores range from 0 (no pain) to 10 (maximal pain) points;total dose of fentanyl; the total dose of intraoperative fentanyl and cumulative dose of postoperative fentanyl during the 24 h after surgery are measured separately;the time to first use of IV-PCA after surgery;intraoperative dose of remifentanil;the frequency and dose of other analgesics (i.e., flurbiprofen axetil or diclofenac sodium);the incidence of PONV during the 24 h after surgery;the time of first ambulation;the manual muscle test (MMT) results for the quadriceps muscle during day 1 of postoperative rehabilitation;perioperative complications related to surgical or anesthetic procedures (i.e., wound infection, bleeding, dislocation, reoperation, nerve injury, hypotension, or falling);days in hospital.

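### Two intraoperative opioid outcomes are poorly defined for detecting a block effect: total fentanyl appears to count the pre-block induction dose, and remifentanil as written depends only on weight and time

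*Protocol article*

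**What the plan says.** Section 2.8.2 of the protocol article sets the fentanyl outcome in one clause: "the total dose of intraoperative fentanyl and cumulative dose of postoperative fentanyl during the 24 h after surgery are measured separately". It gives no starting point for the intraoperative total and does not say whether the induction dose counts. A separate item in the same list is "intraoperative dose of remifentanil", with no unit and no adjustment for weight or duration.

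Section 2.7.1 fixes how these drugs are given:

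- Induction: "General anesthesia will be induced with propofol 1.5 mg/kg, fentanyl 3 μg/kg, and rocuronium 0.6 mg/kg".
- Maintenance: "General anesthesia will be maintained using desflurane 3%–5% and remifentanil 0.2 μg/kg per min". Desflurane has a range; remifentanil has one rate.
- Discretion: "The concentration of desflurane and additional use of rocuronium will be left to the discretion of the attending anesthesiologist". Remifentanil is not named.
- Response to a rise in blood pressure of more than 20% over baseline: "the anesthesiologist will administer fentanyl 50–100 μg and observe the patient for 15 min". A fall is met with ephedrine or phenylephrine. Neither response mentions remifentanil.

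Section 2.7.2 gives the order of events: "After general anesthesia induction, anterior QLB will be performed in the lateral position".

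**The concern.** An outcome meant to show what the block does should consist of quantities that the block can change.

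**Fentanyl.** The induction dose is given before the block, by the same rule in both arms, and varies only with body weight. Counted in the total, it adds variance and no signal. The later increments triggered by blood pressure can respond to the block.

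**Remifentanil.** If section 2.7.1 is followed to the letter, two patients of equal weight with equal infusion times receive identical amounts, however well the block works. A comparison between arms then tests chance differences in body size and duration.

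The stake is interpretation. A difference in remifentanil, or the lack of one, could be read as evidence about opioid sparing when it carries none. A real difference in fentanyl could be missed a little more often than necessary.

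**Working it through.** **The plan's own figure.** Section 2.11 uses a 10-point difference, SD 20, two-sided alpha 0.05 and power 0.80. The normal formula gives n = 2 × (1.960 + 0.842)² × (20/10)² = 62.8, so 63 per group, as stated; 63/0.9 = 70 enrolled. The t-based solution is 63.8, a trivial difference. This sizing concerns QoR-40 only and does not depend on the present point.

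**Size of the induction dose.** The document gives no body weights, so 50–70 kg is assumed.

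| Weight (kg) | Induction fentanyl, 3 μg/kg | In 50 μg increments | In 100 μg increments |
|---|---|---|---|
| 50 | 150 μg | 3.0 | 1.5 |
| 60 | 180 μg | 3.6 | 1.8 |
| 70 | 210 μg | 4.2 | 2.1 |

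The part that cannot respond may thus be as large as several of the increments that can.

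**Effect on precision.** The induction dose has SD = 3 × weight SD, which is 24, 30 or 36 μg for an assumed weight SD of 8, 10 or 12 kg. If post-block fentanyl is unrelated to weight, total SD = √(post-block SD² + induction SD²). The expected difference between arms does not change. With 63 per arm, an assumed 40 μg difference, weight SD 10 kg and the two-sided t test at 0.05 (noncentral t):

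| Post-block SD (μg) | Total SD (μg) | Power, post-block only | Power, total |
|---|---|---|---|
| 60 | √(60² + 30²) = 67.1 | 0.960 | 0.913 |
| 75 | √(75² + 30²) = 80.8 | 0.844 | 0.787 |
| 90 | √(90² + 30²) = 94.9 | 0.697 | 0.651 |

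The loss is about 5 percentage points.

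A second set of assumptions shows the range. Take a true effect of 0.5 SD on post-block fentanyl (power 0.80 by the normal formula) and weight SD 8–15 kg. Power with the total dose is then:

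- 0.73–0.78 for a post-block SD of 100 μg;
- 0.67–0.76 for 75 μg;
- 0.55–0.72 for 50 μg.

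The loss is greatest where the increments vary little compared with the induction dose.

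**Remifentanil.** At the stated rate, dose = 0.2 × weight × minutes. Per hour this is 0.2 × 50 × 60 = 600 μg at 50 kg and 0.2 × 70 × 60 = 840 μg at 70 kg. For independent weight 60 ± 10 kg and time 120 ± 30 min (assumed), the mean is 0.2 × 60 × 120 = 1,440 μg. The variance is 0.2² × (60² × 30² + 120² × 10² + 10² × 30²) = 0.04 × 4,770,000 = 190,800, so the SD is about 437 μg, all of it from weight and duration. A simulation with the same weight and duration distributions in both arms (58 ± 10 kg and 110 ± 25 min, assumed; 63 per arm) rejected in 4.9% of runs. That is the nominal error rate and nothing more.

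**The case against.** **Inclusion of the induction dose is not stated.** Section 2.7.1 separates induction from fentanyl given during surgery for blood pressure, and the abstract describes fentanyl in those terms too. The authors may mean only the later doses, and a counting rule is something an article may leave to the full protocol. This stands in part: inclusion is the plain reading of a total intraoperative dose, not the only one. Fixing the start point settles the matter under either reading.

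**A reader might infer that the fentanyl outcome cannot measure the block, or is biased.** The document does not support that. The 50–100 μg increments are in the total and can respond, and randomization balances the induction dose in expectation. What is lost is precision.

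**A reader might also infer that the remifentanil rate is known to be non-adjustable.** It is not. The fixed rate is inferred from a single value and from remifentanil's absence among the discretionary agents; no sentence forbids a change. Listing the dose as an outcome may suggest that the authors expected it to vary with response, although weight and duration alone would make it vary. The conclusion on remifentanil therefore applies to the text as written.

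**The numbers are assumed.** True: the weights, SDs, durations and the 40 μg effect are not in the document. The trial claims no power for these outcomes, and fentanyl totals built from a few increments may be non-normal, in which case section 2.12 would use the Mann–Whitney test. The direction of the effect does not depend on these choices; its size does.

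**The harm is limited.** Section 2.8.2 does not call either item a measure of opioid sparing, and the abstract's secondary outcomes do not name remifentanil. A delivered dose can be useful description, and false positives are not inflated. This is right, and it is why descriptive reporting is an adequate remedy for remifentanil.

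**Conclusion.** The point holds for two secondary outcomes, to different degrees.

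- **Fentanyl:** diluted, with an undefined start point. If the induction dose is counted, power drops by about 5 points in the central scenarios (0.84 to 0.79 at a post-block SD of 75 μg). Across the second set of assumptions it drops from 0.80 to between 0.55 and 0.78. There is no bias.
- **Remifentanil:** uninformative about analgesia if section 2.7.1 is followed as written. If the rate is titrated in practice, section 2.7.1 is incomplete. In either case sections 2.7.1 and 2.8.2 need to be reconciled.

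The primary QoR-40 analysis and the sample size of 63 (70 enrolled) per group are unaffected.

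**What to change.** 1. **Fentanyl.** In section 2.8.2, define the outcome as fentanyl in μg given from block injection to the end of surgery, and report the induction dose separately. Keep it in μg: the increments are absolute amounts, and dividing them by weight would put weight-driven variation back.
2. **Remifentanil.** State in section 2.7.1 whether the rate is fixed or adjustable. If fixed, report the dose descriptively and do not interpret it as an opioid-sparing comparison. If adjustable, say so and compare the mean rate in μg/kg/min.

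The cost is a change in outcome wording. Section 2.4 keeps the allocation sequence concealed until the final analysis report is complete, so the change can be made blind to allocation, and it should be dated. It relies on the anesthetic record showing when each dose was given, which is assumed because the article does not say so. No change to any dose or to the conduct of anesthesia is proposed.

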### 2.12. Statistical analysis

Statistical analysis will be performed with R software, a free language and software environment for statistical computing and graphics. All statistical tests will be two-sided, and the level of significance will be set at 0.05. First, continuous data will be analyzed by using the Shapiro–Wilk test to confirm normal distribution. Data with a normal distribution will be expressed as mean ± SD and tested by Student’s *t* test. Data without normal distribution will be expressed as median and interquartile range and tested by the Mann–Whitney *U* test. Categorical data will be tested by using the Fisher’s exact test.

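### Time to first IV-PCA use can be right-censored, but the stated analysis gives it only a t test or Mann–Whitney test and no rule for patients who never use PCA

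*Protocol article*

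**What the plan says.** Section 2.8.2 of the protocol article (Secondary outcomes) names "the time to first use of IV-PCA after surgery" with no observation window and no value for a patient who has no first use.

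Section 2.7.3 describes the pump: "A bolus injection of 10 μg fentanyl with a 10-min lockout time may be administered for analgesia", and "continuous infusion of fentanyl will not be considered". Scheduled acetaminophen runs alongside; it "will be administered after the end of surgery and repeated each 6 h until 24 h". Flurbiprofen axetil or diclofenac can also be given for pain.

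Section 2.12 sorts continuous data by a Shapiro–Wilk test. One branch reads "Data with a normal distribution will be expressed as mean ± SD and tested by Student’s" t test; the other reads "Data without normal distribution will be expressed as median and interquartile range and tested by the Mann–Whitney" U test. Categorical data go to Fisher's exact test. The abstract names the same three tests. No time-to-event method appears anywhere.

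**The concern.** Every dose from the pump starts with a patient pressing a button, and other analgesics are given in parallel. Zero use is therefore possible, and for such a patient all that is known is that first use did not occur while the pump was observed. That is a right-censored time. Under section 2.12 a time can only be treated as ordinary continuous data, and neither continuous branch says what to enter for someone without an event.

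The easiest default in software is to treat the value as missing. If the block works, never-users should be more common in the block arm, so dropping them would remove that arm's best results and compare two groups selected after randomisation. Because the choice among dropping, imputing, ranking last and censoring is open, the same data could give different conclusions depending on a decision made at analysis.

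**Working it through.** **Inputs from the article.** Two-sided alpha 0.05 (section 2.12). A 10-point difference, SD 20, power 0.80, 63 per group and 70 with dropouts (section 2.11). A 24 h window for cumulative postoperative fentanyl (section 2.8.2).

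**Inputs that are assumed.** Never-user shares, users' times and their distribution. The article gives none of these.

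**Step 1: the plan's own figure.** n per group = 2 × (1.960 + 0.842)² × 20² / 10² = 2 × 7.85 × 4 = 62.8, so 63. With 10% dropout, 63 / 0.90 = 70. Both reproduce. They concern QoR-40 only; 63 is used below as the arm size.

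**Step 2: what dropping does to the estimate.** Let p be the never-user share and m the median among users, with exponential times. The median M in all patients solves p + (1 − p) × 2^(−M/m) = 0.5.

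- 5% vs 20%, users' medians 2 h vs 3 h. Control: 2^(−M/2) = 0.45/0.95 = 0.474, M = 2.16 h. Block: 2^(−M/3) = 0.30/0.80 = 0.375, M = 4.25 h. The difference in all patients is about 2.1 h; users only show 1.0 h.
- 2% vs 10%, 2 h vs 3 h. Control: 0.48/0.98 = 0.490, M = 2.06 h. Block: 0.40/0.90 = 0.444, M = 3.51 h. The difference is about 1.45 h; users only show 1.0 h.

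**Step 3: power by simulation.** 63 per arm, exponential users' times capped at 24 h, never-users drawn at random, 1,500 to 2,000 trials per scenario (simulation error about ±0.02):

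| Never-users (control vs block); users' medians | Mann–Whitney, users only | Mann–Whitney, never-users tied last | Log-rank, censored at 24 h |
|---|---|---|---|
| (a) 5% vs 20%; 2 h vs 2 h | 0.05 | 0.29 | 0.57 |
| (b) 5% vs 20%; 2 h vs 3 h | 0.44 | 0.84 | 0.92 |
| (c) 2% vs 10%; 2 h vs 3 h | 0.46 | 0.70 | 0.84 |

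**Step 4: another effect model.** Exponential times observed for 24 h, hazard ratio 0.6, 3,000 trials per row:

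| Never-users (control, block) | Users only | Tied last | Log-rank |
|---|---|---|---|
| about 0%, about 0% | 0.68 | 0.69 | 0.82 |
| 2%, 10% | 0.46 | 0.69 | 0.79 |
| 5%, 17% | 0.34 | 0.69 | 0.77 |
| 10%, 25% | 0.22 | 0.67 | 0.74 |
| 20%, 38% | 0.13 | 0.62 | 0.67 |

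With no true effect, every method rejects in about 5% of trials. The harm is lost power and an understated delay, not false positives.

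**Step 5: when it hardly matters.** With never-users at 1% vs 3% and medians of 2 h vs 3 h, Mann–Whitney on users only has power 0.49 against 0.56 with never-users ranked last.

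**The case against.** A reader might infer that the plan excludes never-users. It does not say so; the article is silent, and exclusion is only one possible default. Nor is Mann–Whitney unusable here. If every non-user is censored at one common time, each ranks above every observed time, and Mann–Whitney with non-users tied at the top is valid. In that case it is Gehan's generalised Wilcoxon test. It fits section 2.12 as written and recovers most of the loss in scenarios (b) and (c). This stands, but it needs a common window and a ranking rule, and the article states neither.

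Never-users may also be rare. The background section describes pain after this surgery as moderate to severe, and the block is a single injection. Step 5 shows that the loss is then small. Part of the log-rank advantage also comes from the assumed exponential times: with no never-users and medians of 2 h vs 3 h, log-rank gives 0.60 against 0.49 for Mann–Whitney. Both points stand and limit the size of the claim.

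The coding of non-users could be left to an analysis plan that is not shown. That answers the missing value in part. It does not answer the method, because the article itself sends every continuous variable to one of two tests that make no provision for censoring.

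It is tempting to extend the point to "the time of first ambulation". The article gives no sign that patients would leave hospital without walking, and censoring at discharge could be informative because discharge may depend on mobility. That extension is not made.

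**Conclusion.** The point holds as a mismatch between an outcome that can be censored and the only tests the article offers for it. If never-users were dropped, power would be about 0.45 in scenarios (b) and (c), against 0.70–0.85 with never-users ranked last and 0.84–0.92 with log-rank, and the difference in medians would shrink from about 1.45–2.1 h to 1.0 h. These figures rest on assumed never-user shares, medians and exponential times.

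A reader might go further and conclude that the plan necessarily hides a real block effect. The documents do not support that. It would require never-users to be dropped and also not to be rare. Even then, (b) and (c) show an effect weakened rather than removed. Only (a) shows no signal, and it assumes that the block raises never-use without delaying anyone else's first bolus.

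This is one of ten secondary outcomes. The QoR-40 analysis and sample size are untouched, and cumulative 24 h fentanyl counts a never-user's PCA dose as zero, so part of the opioid-sparing effect is captured there.

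**What to change.** Add to section 2.12 that time to first IV-PCA use is analysed in all randomised patients over a fixed window of 24 h after surgery, the window section 2.8.2 already uses for postoperative fentanyl. Censor non-users at 24 h, show Kaplan–Meier curves, and compare the arms with a log-rank test. Report the number of never-users in each arm.

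If the investigators prefer to stay with the listed tests, the minimum is Mann–Whitney with never-users tied at the top rank. In either case, rule out dropping non-users, and rule out the t test for this outcome because it needs an arbitrary number for each of them.

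The cost is a sentence or two and one more analysis method for a secondary outcome. Sample size and design do not change. The article reports recruitment as ongoing and keeps the allocation sequence concealed until the final analysis report, so the rule can be set before anyone sees results by arm.
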